## 8 STUDY INTERVENTION

### 8.1 Identity of Investigational Products (treatment / medical device)

VPS placement by US-G or stereotactic navigation.

#### 8.1.1 Experimental Intervention (treatment / medical device)

- US: navigation: BK Medical 5000 with burr hole probe (Type 9063 N11C5S, 11-5MHz)

#### 8.1.2 Control Intervention (standard/routine/comparator treatment / medical device)

Stereotactic navigation: Brainlab Dual Curve System (cranial navigation software version 3.1.)

#### 8.1.3 Packaging, Labelling, and Supply (re-supply)

- N/A

#### 8.1.4 Storage Conditions

- N/A

## 8.2 Administration of experimental and control interventions

### 8.2.1 Experimental Intervention

At our institution, we routinely insert a (right) frontal VPS, while rarely an occipital VPS is placed. Since 2014, the abdominal shunt placement is performed by a visceral surgeon using the laparoscopic technique. The "Kocher entry point" (measured at 11-12cm from Nasion and 3-3.5cm lateral to the midline) is used as the frontal entry point, the "Trigunum entry point" (measured at 4cm behind, and 5.5cm above the external auditory canal) is used as the occipital entry point. All catheters are connected to a burr-hole reservoir, a programmable valve (Codman Hakim®, Integra LifeSciences, USA), and a distal peritoneal catheter (Figure 2).

There is no pre-planning before starting the operation. After intubation, the head of the patient is placed on a horseshoe head holder slightly rotated to the contralateral side of the operation (Figure 3). There is no need to register the navigation.

Patients in the US cohort need to have a CT or MR scan not older than 90 days old (counted back from the operation day).

Directly before the operation, the distal shunt parts (peritoneal catheter, valve, and burrhole reservoir) are connected to each other and connections are saved with sutures.

After skin incision a large burr hole is placed with a 14-11mm high speed drill (Figure 4) at 12cm from Nasion and 3cm lateral to the intended side of shunt placement. Lateral enlargement of the burr hole is done until passing of the catheter through the adapted guide-channel lateral to the US burr hole probe is possible. US-G (BK Medical 5000, bk medical Medizinische Systeme GmbH, Quickborn, Germany) VPS placement is done using a burr hole probe (type 9063 N11C5S, 11-5 MHz) onto which a sterile single-use guide channel, adaptable for different catheter diameters is mounted (Figure 5 and 6).

Following dural opening, real-time US navigation is done holding the US probe in the coronal plane (Figure 7), showing a cross-section through both frontal horns. Saline irrigation is applied to achieve better contrast. The inline trajectory (Figure 7, in yellow) is used as guidance for positioning of the ventricular catheter with the tip at the foramen of Monro, then Foramen Monro and Choroid plexus are visualized, and the catheter is inserted. After positioning of the proximal catheter, under real-time visualisation (Figure 8), the US probe is removed, the catheter is shortened and connected to the burr-hole reservoir. The remaining procedure is similar to any other VPS placement, where the valve is connected to the burr hole device and the distal catheter, which is then implanted laparoscopically into the abdomen.

The physicians are already trained in the use of the US burr hole probe since it has been in use for many other operations, and VPS as well as EVD placement before. The operation will be performed by a trained neurosurgeon or by an advanced resident under supervision.

[figure not shown]

Figure 2: Connection of the valve and the peritoneal catheter to a large burr hole reservoir.

Figure 3: Positioning and covering of the patient for standard right frontal VPS placement (head left, abdomen right).

Figure 4: Placement of the burr hole, enlargement to the lateral side.

[figure not shown]

Figure 5: US burr hole probe attached to the guidance tool for the ventricular catheter, adaptable for the exact diameter of catheter (disposable material, single-use).

Figure 6: Image of the diameter of the US burr hole probe together with the attached guidance.

Figure 7: Real-time US navigation showing a coronal plane presenting both frontal horns of the lateral ventricles and the trajectory for catheter placement (in yellow).

Figure 8: Real-time US navigation showing a coronal plane presenting the catheter (hyperintense) entering the ventricle along the trajectory (in yellow).

### 8.2.2 Control Intervention

Patient in the stereotactic group need to have a CT scan that is not older than 5 days counted backwards from the operation day.

The exact location of the entry point, the trajectory, and the length of the catheter will be pre-planned on the newest CT at a Brainlab Workstation using cranial navigation software version 3.1. (Brainlab AG, Munich, Germany). After intubation the head of the patient will be fixed in a Mayfield head clamp slightly rotated to the contralateral side of the operation. Before starting the operation, the navigation will be registered. After that the incision will be marked at the pre-planned entry point. The distal shunt parts are also connected directly before the start of the operation.

For placement the ventricular catheter will be inserted with the navigated stylet exactly along the planned trajectory. After functional control the catheter is cut in the precalculated length, and connected to the distal shunt parts. The other steps of the operation are exactly the same as described above for US-G VPS placement.

The physicians are already trained in using the Brainlab navigation since it is in use for almost every craniotomy and for biopsies. The operation is performed by a trained neurosurgeon or by an advanced resident under supervision.

### 8.3 Dose / Device modifications

- In case of very small ventricular width based on the surgeon's individual judgement one can decide to use stereotactic navigation instead of US navigation. Due to preoperative planning and necessity of a CT scan at admission this crossover has to be done preoperatively. Vice versa, there is the possibility to intraoperatively crossover from stereotactic navigation to US navigation in case of unsuccessful placement with stereotactic navigation (e.g. in cases with new mass effect compared to the preoperative CT scan and distorted ventricular anatomy).

### 8.4 Compliance with study intervention

During the perioperative period, compliance to the randomized navigation method will be monitored by study nurses. In cases of switched navigation method pre- or intraoperatively (see 8.3.) the reasons will be recorded and there will be an intention-to-treat analysis.

### **8.5 Data Collection and Follow-up for withdrawn participants**

Withdrawn patients will be clinically followed up as non-participants, 6-8 weeks postoperatively in our outpatient clinic. A second follow-up will be performed 6 months postoperatively including a native CT scan.

### **8.6 Trial specific preventive measures**

There are no specific restrictions associated with either navigation method. Patients sensitive to radiation (e.g. pregnant women or children) are excluded from the study (see eligibility criteria 7.1.) due to follow-up with CT scan. To our knowledge there are no contraindications for US of the brain, and no harmful side effects of US are described in the literature.

### **8.7 Concomitant Interventions (treatments)**

- N/A

### **8.8 Study Drug / Medical Device Accountability**

The devices for both of the navigation method (Brainlab stereotactic navigation system and BK 5000 medical US system) are stored in an equipment room in the OR tract of the university hospital of Basel. Brainlab planning workstation is located in the library of the university hospital of Basel.

All the equipment is reusable and partly sterile (e.g. US burr hole probe and reference star for the stereotactic navigation).

### **8.9 Return or Destruction of Study Drug / Medical Device**

- Return or destruction of either medical device is according to standard procedures.

## 9 STUDY ASSESSMENTS

### 9.1 Study flow chart / table of study procedures and assessments

| Study Periods                                | Screening Admission                                         | Treatment, Intervention Period |                                                                                 |                                       | Follow-up          |                                         |
|----------------------------------------------|-------------------------------------------------------------|--------------------------------|---------------------------------------------------------------------------------|---------------------------------------|--------------------|-----------------------------------------|
| Visit                                        | 1                                                           | 2                              | 3                                                                               | 4                                     | 5                  | 6                                       |
| Time (hour, day, week)                       | 1 day preop.                                                | Operation day                  | 2-5 days post-op. (48-120h)                                                     | At discharge (approx. 7 days postop.) | 6-8 weeks post-op. | 6 months postop. (150-210 days postop.) |
| Patient Information and Informed Consent     | x                                                           |                                |                                                                                 |                                       |                    |                                         |
| Randomization                                | x                                                           |                                |                                                                                 |                                       |                    |                                         |
| Demographics (age, sex)                      | x                                                           |                                |                                                                                 |                                       |                    |                                         |
| In- /Exclusion Criteria                      | x                                                           |                                |                                                                                 |                                       |                    |                                         |
| Neurologic examination                       | x                                                           |                                | x                                                                               | x                                     | x                  | x                                       |
| cCT scan                                     | (x stereotactic navigation group, 1 to 5 days preoperative) |                                | x
(2 nd to 5 th day or earlier if neurologic symptoms) |                                       |                    | x                                       |
| Medical history                              | x                                                           |                                |                                                                                 |                                       |                    |                                         |
| Primary outcome (Surgical intervention time) |                                                             | x                              |                                                                                 |                                       |                    |                                         |
| Secondary Outcomes                           |                                                             | x                              | x                                                                               | x                                     | x                  | x                                       |
| VPS dysfunction                              |                                                             | (x)                            | x                                                                               | x                                     | x                  | x                                       |
| Operative Revision and reasons               |                                                             | (x)                            | x                                                                               | x                                     | x                  | x                                       |
| Operation and anaesthesia time               |                                                             | x                              |                                                                                 |                                       |                    |                                         |
| Number of puncture attempts                  |                                                             | x                              |                                                                                 |                                       |                    |                                         |
| Complications                                |                                                             | x                              | x                                                                               | x                                     | x                  | x                                       |
| Hospitalisation time (days)                  |                                                             |                                |                                                                                 | x                                     |                    |                                         |
| ICU time (days)                              |                                                             |                                |                                                                                 | x                                     |                    |                                         |
| Discharge destination                 |                                                             |                                |                                                                                 | x                              |                    |                                         |
| Adverse events                               |                                                             | x                              | x                                                                               | x                                     | x                  | x                                       |
| Death                                 |                                                             | x                       | x                                                                        | x                              | x           | x                                |

## 9.2. Assessments of outcomes

### 9.2.1. Assessment of primary outcome

Primary outcome (surgical intervention time) will be recorded for every operation by anaesthesiology, as it is standard in our department. This time spans the time spent in the OR by the neurosurgeon, beginning with any intervention on the patient (e.g. positioning, head clamping) and ends when the neurosurgical part of the operation is finished, so it consists of the preparation time, and the operation time of the neurosurgical part of the operation together. To minimize bias, the visceral surgery part of the operation (laparoscopically assisted insertion of the peritoneal catheter intraperitoneally) will not be included into this time interval.

[figure not shown]

**Figure 1: Composition of the surgical intervention time (preparation time plus operation time neurosurgical part), plus additional five minutes in the stereotactic navigation group.**

### 9.2.2. Assessment of secondary outcomes

Operation time and anesthesia time in minutes: these times will be assessed at the operation day by anaesthesiology

Number of puncture attempts: this will be assessed at the operation day by the operating surgeon

Catheter placement (optimal vs. not optimal): between the 2nd and 5th postoperative day a CT scan will be made and VPS positioning will be assessed. Optimal catheter placement is defined as free-floating within the CSF without touching the ventricle wall or septum pellucidum, and the tip of the catheter located at the foramen of Monro showing an optimal length of the catheter. Catheters that did not fulfil all criteria have been defined as not optimal placed. Positioning of catheters will be further graded according to Yim et al. into grades I to IV (grade I: catheter terminates in the ipsilateral frontal horn, grade II: catheter terminates in contralateral frontal horn, grade III: catheter terminates in non-targeted CSF spaces, grade IV: catheter terminates intraparenchymally).

The cCT scan will be repeated during second follow-up after 6 months. This outcome will be assessed by partially blinded neuroradiologists.

Volumetry of side ventricles pre- and postoperatively in cm^3 (number and relative change): This will be assessed on the pre- and postoperative CT scans by partially blinded neuroradiologists.

Evan's Index pre- and postoperatively (number and relative change): This will be assessed on the pre- and postoperative CT scans by partially blinded neuroradiologists.

Complications (infection, bleeding, complications ass. with navigation method), mortality: rate and detail of complications will be assessed directly postoperative during the whole hospitalisation time and during the 1st and 2nd follow-up by the study nurse, the same accounts for mortality (including the reason for death if known).

Revision surgery (yes/no) and reason for revision: the rate of revision surgery as well as the indication for revision will be reported by the study nurse.

VPS dysfunction: the rate of VPS dysfunction will be assessed directly postoperative during the whole hospitalisation time, and during the 1st and 2nd follow-up by the study nurse.

### 9.2.3 Assessment of other outcomes of interest

- N/A

### 9.2.4 Assessment of safety outcomes

#### 9.2.4.1 Adverse events

- Adverse events in our study mean death due to any reason (related or unrelated to the study) and any complications referable to any of the navigation methods (e.g. headholder complications for the stereotactic navigation method, local bleeding at the burr hole for the US navigation method (due to enlarged burr hole).

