### 3. BACKGROUND AND RATIONALE

#### 3.1 Background and Rationale

- VPS placement is one of the most frequent procedures in neurosurgical practice and is done approximatively once per week in our clinic (40 to 50 cases per year). The indications vary from normal pressure hydrocephalus in elderly patients to VPS-dependency after subarachnoid hemorrhage, infection or trauma, mostly in younger patients. The position of the proximal ventricular catheter is important since it influences the possible malfunction of the VPS. With freehand placement rates of malpositioned VPS are still high.

For the improvement of accuracy in proximal VPS placement, navigation-based insertion techniques have been developed. VPS placement using stereotactic navigation has shown a high accuracy of catheter placement, while the main limitations are that for referencing, the head of the patient needs to be fixed in a head holder and the preoperative set-up can be time-consuming. US-G VPS placement using a burr hole probe was described as an alternate for image-guided VPS placement technique. For US-G VPS placement head fixation or preoperative registration is not needed. Initially, the entry point is measured according to standard anatomical landmarks, thereafter the catheter is placed into the ventricle under real-time US guidance along the depicted trajectory. To date, most of the clinical evidence regarding image-guided VPS placement derives from small retrospective cohort studies.

Installation and use of image guidance techniques add extra time to the standardized procedure of VPS placement, leading to longer operation times, and higher costs. Besides that patients will be anesthetized for a longer time, leading to possible complications of prolonged anesthesia. An ideal image guidance technique should, therefore, be easy to handle, and not too time-consuming.

The rationale of this study is to prospectively compare US-G VPS placement to stereotactic navigation in a randomized controlled fashion with the surgical intervention time as a primary outcome.

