## 10 SAFETY

### 10.3 Medical Device Category A studies

Device deficiencies and all adverse events (AE) including all serious adverse events (SAE) are collected, fully investigated and documented in the source document and appropriate case report form (CRF) during the entire study period, i.e. from patient's informed consent until the last protocol-specific procedure, including a safety follow-up period. Documentation includes dates of event, treatment, resolution, assessment of seriousness and causal relationship to device and/or study procedure [ISO 14155, 6.4.1.4].

For this study these are especially perioperative complications of VPS implantation and perioperative complications of either navigation method (e.g. headholder complications such as bleeding or infection for the stereotactic navigation and local bleeding at the burr hole due to enlargement for the US navigation).

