#### 10.3.1 Definition and Assessment of safety related events

##### Adverse Event (AE)

Any untoward medical occurrence, unintended disease or injury or any untoward clinical signs (including an abnormal laboratory finding) in participants, users or other persons whether or not related to the investigational medical device [ISO 14155: 3.2].

Complications related to the operation and either of the navigation method will be reported and patient will receive the appropriate monitoring and, if necessary, treatment.

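### Protocol 9.2.4.1 and 10.3/10.3.1 define an adverse event differently, so AE and SAE counts depend on which section staff follow

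*Combined protocol and SAP*

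**What the plan says.** The protocol sets the scope of an adverse event in three places.

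- **Section 9.2.4.1**, under the assessment of safety outcomes, says that adverse events in this study "mean death due to any reason (related or unrelated to the study) and any complications referable to any of the navigation methods". Its examples differ by arm: head-holder complications for stereotactic navigation, and local bleeding at the enlarged burr hole for ultrasound.
- **Section 10.3** says that "all adverse events (AE) including all serious adverse events (SAE) are collected, fully investigated and documented", from informed consent to the last protocol procedure and including a safety follow-up. Documentation covers dates, treatment, resolution, seriousness and causal relationship. It adds: "For this study these are especially perioperative complications of VPS implantation and perioperative complications of either navigation method".
- **Section 10.3.1** defines an AE as "Any untoward medical occurrence, unintended disease or injury or any untoward clinical signs" in participants, users or others, "whether or not related to the investigational medical device". It then says "Complications related to the operation and either of the navigation method will be reported".

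Two analysis provisions use the result. Protocol 11.4.5 promises a detailed between-arm examination of AEs. SAP 6.5 lists safety events by treatment received and compares frequencies only if many AEs occur; 'many' is not defined.

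**The concern.** Section 9.2.4.1 is worded as the definition for this particular study, so staff could reasonably take it as the working rule and read 10.3.1 as general regulatory text. Under that reading a non-fatal event becomes an AE only after someone has judged that it stems from a navigation method. The judgement comes before recording, when it should come after. It is also made with knowledge of the arm and with different example events for each arm.

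Safety is part of the stated main objective in the synopsis and in SAP 1.2. An AE table whose content depends on which section was followed cannot carry that objective well. Differences between arms could partly reflect how events were attributed, and a low total could mean that the SAP comparison is never made.

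**Working it through.** No arithmetic applies. The documents give no AE rate, and the plan states no figure that could be reproduced. The check sets the rules side by side and follows events through them.

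**1. Classification of example events under each rule**

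| Event | 9.2.4.1 | 10.3 / 10.3.1 | Recorded elsewhere? |
|---|---|---|---|
| Death, any cause | AE | AE | Yes, Visits 2 to 6 |
| Bleeding or infection from the head holder | AE | AE | Yes, as a complication |
| Shunt dysfunction or revision not attributed to navigation | Not an AE | AE | Yes, with causes, Visits 2 to 6 |
| New delirium not attributed to navigation | Not an AE | AE | Yes, as a neurological symptom, Visits 3 to 6 |
| Non-fatal thromboembolic event not attributed to navigation | Not an AE | AE | Possibly, as an 'other' complication |

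The rules agree on deaths and navigation complications. They disagree on every non-fatal event that is not attributed to navigation.

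**2. Is there a tie-break?** None was found. The word 'especially' in 10.3 marks emphasis and does not narrow the word 'all' before it. The reporting sentence at the end of the AE definition in 10.3.1 adds a third scope, complications of the operation and of the navigation method. That is wider than 9.2.4.1 and narrower than the definition just above it.

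**3. Effect on SAEs.** Section 10.3.1 defines an SAE as an adverse event that led to one of the listed outcomes. SAEs are therefore a subset of AEs. If the narrow AE rule is used, a non-fatal serious event not attributed to navigation is not an SAE either.

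**4. Who attributes?** Protocol 6.2.2 says the treating physician cannot be blinded. Protocol 9.2.2 has the study nurse assess complications, and 8.4 has study nurses monitor compliance with the randomised method. Both groups know the allocation.

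**5. What survives outside the AE definition?** The operation-day list (9.3.2) records complications with details. Visits 3 to 6 record infection, bleeding, seizure, fracture and an open 'other' category. Intensive-care and hospital days are recorded at discharge. Those visit lists do not ask for the seriousness, causality and resolution data that 10.3 requires for AEs. The secondary complications outcome names infection, bleeding and navigation-associated events. The safety endpoints in 5.4, 11.4.5 and SAP 6.5 name no general medical or anaesthesia event. An 'other' entry is therefore collected, but has no stated route into a between-arm comparison.

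**6. Schedule.** Consent is at Visit 1, one day before surgery. The AE and death rows of both schedule tables start at Visit 2, whereas 10.3 starts collection at consent. On the schedule's own timing the gap is about one day.

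**The case against.** The strongest reply is that 10.3 belongs to the dedicated safety chapter and requires all AEs and SAEs without restriction. Section 9.2.4.1 can then be read as naming events of special interest, and its examples also appear in 10.3. On this reading nothing goes wrong in practice. It is a sensible reading, but the text of 9.2.4.1 says what adverse events mean in the study, not which ones are of special interest, so the reading cannot be relied on.

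A reader might go further the other way and infer that events outside 9.2.4.1 are lost from the trial data. The documents do not support that. Complications, dysfunction, revision, delirium and length of stay are recorded without using the AE definition. Pneumonia could be entered under infection, which the complication lists do not limit to shunt infection, although 6.1 mentions shunt infections at follow-up. What is at risk is classification and assessment as an AE or SAE. The case report form is not among the documents, so it may collect more than the visit lists show.

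A reader might also infer that the trial would miss the very harm it aims to reduce, because 3.1 says "Besides that patients will be anesthetized for a longer time, leading to possible complications of prolonged anesthesia". That is one background reason, given alongside longer operations and cost. The hypothesis in 11.1 concerns surgical intervention time, and no endpoint measures anaesthesia harm.

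Finally, 'referable' could be stretched to cover harm from a longer set-up, so exclusion of such events under 9.2.4.1 is likely but not certain. That ambiguity is itself a reason to settle the wording.

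**Conclusion.** The contradiction is certain from the text. Two operative definitions of an adverse event stand in the protocol, and no sentence ranks them. The consequence is conditional on 9.2.4.1 being followed: non-fatal events not attributed to navigation, including possible anaesthesia or general medical complications, would not be assessed as AEs or SAEs, and the AE comparisons in 11.4.5 and SAP 6.5 would depend on that choice. Because the study has a single centre, the risk is inconsistent recording among its staff, not differences between sites.

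The size in patients cannot be given. Any number would rest wholly on an assumed event rate, and some of the events counted would have other recording routes. The primary endpoint and its analysis are unaffected. The point should be corrected because safety is a stated objective and the correction is cheap.

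**What to change.** - Replace the definition in 9.2.4.1 with a cross-reference to 10.3/10.3.1: all AEs regardless of relationship, over the collection period in 10.3, with relatedness assessed after the event is recorded. Reconcile the reporting sentence in 10.3.1 with this.
- Keep navigation-related complications as a named subset of AEs.
- State in 11.4.5 and SAP 6.5 how recorded complications, including 'other' entries, map to AEs for the between-arm comparison. The existing 'other' field is enough; no new form category is needed.
- Align the AE and death rows in both schedule tables with the start at consent.
- If recruitment is already complete (the synopsis planned the last participant out for 02/2025), state in the SAP and the report which definition was applied. Review the 'other' entries against the 10.3.1 definition before database lock.

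The cost is wording changes and some additional AE entries, which 10.3 already requires. A late review can classify only what was written down at the time, so it repairs the problem only in part.
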